## Abstract

**Simple Summary:**

Risk of falls secondary to osteoporosis consists an important problem that affects society and there is no defined treatment to ameliorate both the symptoms and quality of life of elderly women with osteoporosis and reduce the risk of falls. We aim to evaluate the effectiveness of whole-body vibration protocol combined with various exercises specifically in this population, therefore, our results might identify a defined protocol to reduce their risk of falls as strength, balance, and functional capacity improves.

**Abstract:**

Osteoporosis and the risk of falls increase the risk of fractures and events of falls. Prescriptions and programs for different forms of exercise have different impacts on the risk of falls, and exercises from multiple categories of whole-body vibration can be effective. This study aims to evaluate the effectiveness of whole-body vibration (WBV) protocol combined with multicomponent training (MCT) in elderly women with osteoporosis and their history of falls. Our proposal is a protocol for a randomized clinical trial, divided into two stages: First, development of a protocol for WVB combined with MCT for elderly women with osteoporosis and a history of falls, under the Guidelines of the American College of Sports Medicine, and following the recommendations of the Standard Protocol Items Recommendations for Interventional Trials (SPIRIT), and second, a randomized controlled clinical trial following the Consolidated Standards of Reporting Trials (CONSORT). This trial will have implications for the effectiveness of a vibration protocol combined with multicomponent exercise on the risk of falls and quality of life for older women with osteoporosis. We expect that adding full-body vibration to an exercise protocol will decrease the risk of falls and improve participants’ quality of life, as well as their strength, balance, and functional capacity.

## 1. Introduction

According to the World Health Organization (WHO), osteoporosis (OST) is defined as the loss of bone mineral density exceeding −2.5 standard deviations (T-score) concerning young adults [1]. About 200 million people worldwide have OST [2] and, with the growth of the elderly population, by the year 2050, we expect an increase of up to three times in the risk of having OST [3]. OST is considered a systemic disease whose main alterations are the decrease in bone mass and strength, with deterioration of the bone microarchitecture, increasing the chances of fractures. Women are more susceptible to OST than men, because, in addition to menopause and estrogen deficiencies, they have lower bone mineral density, leading to a greater risk of falls and imbalance problems [4]. In addition to the bone loss, other functional declines associated with aging may be present [5], such as the risk of falls, muscle strength, gait, balance, and vision that should be included in OST assessment in elderly women [6].

Women with OST have intrinsic factors that increase their risk of falls [7]. For this reason, several studies [8,9,10,11,12,13,14] investigate the effects of different therapeutic modalities in preventing the risk of falls and improving the perception of quality of life in elderly women with OST.

Studies [15,16,17] indicate that multicomponent exercises reduce the incidence and risk of falls and present few adverse events for the elderly population.

Data from a meta-analysis [18] show that long term effects of exercise reduce the risk of falls (RR 0.88; 95% CI, 0.79–0.98; 4420 participants, 20 randomized controlled trials; moderate heterogeneity) and fall injuries (RR 0.74; 95% CI, 0.62–0.88; 8410 participants, nine RCTs; moderate but not substantial heterogeneity) in the elderly. This study also points out that the most used exercises are multicomponent training (MCT), three times a week, with an average of 50 min per session. Similarly, another review [19] shows that the MCT, among them the functional ones and the balance and resistance ones, reduce the rate of falls by 34% (RaR 0.66, 95% CI 0, 50 to 0.88; 1374 participants, 11 studies; evidence of moderate certainty) and reduce the number of people experiencing one or more falls by 22% (RR 0.78, 95% CI 0.64 to 0.96; 1623 participants, 17 studies; evidence of moderate certainty).

Another therapeutic modality used in people with OST is whole-body vibration (WBV), a non-invasive and non-pharmacological intervention that can promote a reduction in the impact on bone mass and density, helping to gain balance and muscle strength and reducing the number and risk of falls [20,21,22,23,24]. WBV alone or in combination with exercise can also decrease the number of falls and the risk of falls, being essential to prevent bone fractures and osteoporosis [21,22,25].

In clinical practice, protocols with the prescription of multicomponent exercises and vibration in the elderly and patients with osteoporosis are described in isolation or combination during the use of the platform. To our knowledge, no studies have been found using WBV combined with MCT in elderly women with OST, in which the protocol contained detailed information on parameters, frequency, and duration, among others, necessary for clinical reproducibility. Given the above, the present study aims to develop a protocol for a clinical trial to verify the efficacy of WBV combined with MCT in the risk of falls and the quality of life of elderly women with OST.

## 2. Materials and Methods

### 2.1. Study Design

The following is a methodological type study to create a protocol and carry out a randomized and controlled clinical trial. It was divided into 2 stages: (1) Development of a protocol for WBV combined with MCT, following the Guidelines of the American College of Sports Medicine (ACSM) [26] for elderly women with OST with a history of falls. The protocol was developed following the recommendations of the SPIRIT statement; (2) proposal of a randomized controlled clinical trial following the norms of the Consolidated Standards of Reporting Trials (CONSORT).

#### 2.1.1. Stage 1: Protocol

At this stage, the Guidelines of the American College of Sports Medicine [26] were consulted, aiming to establish the main exercises for elderly people with OST and the risk of falls. Following these guidelines, specific intensity, frequency, exercise modality, and duration parameters were established for the profile of the participants (Table 1 and Table 2).

According to the ACSM guidelines a training program is designed to achieve individual health and fitness goals through the principles of prescribing an exercise routine. They continue to infer the importance of employing the FITT-VP principle of prescribing an exercise routine, which comprises frequency, intensity, time, type, and total volume of progression, based on ACSM evidence. In the context of individuals with clinical problems and with reservations, this prescription is subject to modification. In this context, the protocol followed the FITT Recommendations for elder individuals and with OST, following the ACSM Guidelines for Stress Tests and Prescription [26].

#### 2.1.2. Stage 2: Clinical Trial

We will develop a double-blind controlled clinical trial following the guidelines established in the CONSORT, registered in ReBec (n. RBR-3xdf4k). The following topics refer to the steps to be taken to conduct the clinical trial:

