### 2.5. Blinding

Outcome assessments will be performed by three researchers who are blind to the intervention group to which the participant was allocated. Statistical analysis will also be performed by a researcher who is blind to other research procedures.

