### 2.6. Intervention

The intervention protocol will be applied by an experienced physical therapist, blind to the assessment of outcomes, soon after the enrolment period. It will consist of 8 weeks of training for both groups, totaling 24 sessions distributed three times a week, on alternating days. Each session will last between 45 and 48 min, depending on the participant’s group (Table 3).

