Balance activities will include static and dynamic exercises with the progression of postures as training progresses. All exercises in the program will be performed slowly to ensure the subjects’ safety, emphasizing good posture, social interaction, and pleasure [25].

Participants will perform the WBV on a vibrating platform after the end of the TMC. The vibration training will be carried out on the vibration platform KIKOS P204–110V (São Paulo, Brazil), whose vibration is of the lateral–lateral and oscillatory type. There will be 24 vibration sessions with an incremental increase of progressive frequency from 12.6 Hz to 30 Hz, the oscillation amplitude of 4 mm from peak to peak, lasting 60 s, and with a rest time of 10 to 30 s. Participants must, at the time of vibration, for better fixation of the feet on the board, perform the vibration with a silicone pad for the heels (made of non-slip material), so that only the forefoot and midfoot are in direct contact with the platform, to reduce the transmission of vibrations to the head, and a squat position of 100° will be adopted (considering 180° as total knee extension) in Figure 2. 

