#### 2.6.2. MCT Group Intervention Description

The participants of the control group will only perform the MCT during the 8 weeks, totaling 24 sessions, following the same descriptions of the MCT of the GTMV group.

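### The trial is labelled double-blind, but participants and therapist know the allocation and both primary outcomes are rated by the participant

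*Protocol article*

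**What the plan says.** Section 2.1.2 sets the label: "We will develop a double-blind controlled clinical trial".

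Section 2.5 names who is blinded. On the assessors: "Outcome assessments will be performed by three researchers who are blind to the intervention group". On the analyst: "Statistical analysis will also be performed by a researcher who is blind to other research procedures". Nobody else is named there. Section 2.6 adds that the treating physical therapist is "blind to the assessment of outcomes", which concerns the measurements and not the group.

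The arms differ visibly. In the MCTV group, "Participants will perform the WBV on a vibrating platform after the end of the TMC", and during vibration "a squat position of 100° will be adopted" (section 2.6.1). For the comparator, section 2.6.2 says: "The participants of the control group will only perform the MCT during the 8 weeks". No sham or inactive platform is described. Section 2.6 gives the timing, which depends on group: "Each session will last between 45 and 48 min".

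Section 2.7.1 makes FES-I (16 items on worry about falling) and WHOQOL-OLD (24 items) the primary outcomes. Both are Likert questionnaires completed from the participant's own answers. The Biodex Falls Risk Test and functional reach are secondary (section 2.7.2). The Limitations mention adherence and the lack of an untreated group, but not participant awareness of allocation.

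**The concern.** A reader who sees the label will take participants to be among those blinded and will judge the risk of bias accordingly. Here they cannot be blinded, and they are the raters of both primary outcomes. FES-I measures concern about falling, a state of mind that can move if a woman believes she is getting the enhanced programme, or is disappointed not to be. An assessor who does not know the group only records her answer.

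Two things are at stake: a correct statement of the risk of bias on the outcomes that carry the trial's claim, and a conclusion that goes no further than the comparison actually made.

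**Working it through.** The article states no figure for this point, so there is nothing to reproduce. The check sets the sections side by side and then looks at scale.

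**1. Who knows the group**

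| Role | What the article says | Blind to group? |
|---|---|---|
| Participant | Platform or no platform, no sham (2.6.1, 2.6.2); not named in 2.5 | No, by inference |
| Therapist | Delivers the intervention; kept from outcome assessment only (2.6) | No |
| Three assessors | Blind to group (2.5) | Yes |
| Analyst | Blind to the other research procedures (2.5) | Yes, taking this to include allocation |

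**2. Who rates each outcome**

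- FES-I and WHOQOL-OLD (primary): the participant.
- PGIC (secondary): the participant.
- Biodex index and functional reach (secondary): read off an instrument or ruler by a blinded assessor, although the participant performs the task knowing her group.

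**3. When it matters**

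Table 3 places the first FES-I and WHOQOL-OLD at recruitment, and section 2.4 opens the envelopes only when the intervention starts. Baseline answers are therefore given before the group is known. The reassessments after sessions 8, 16 and 24 come after it is known.

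**4. Scale of the target**

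Section 2.8 targets more than 2.9 FES-I points between groups.

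- 2.9 / 16 items = 0.18 of a category per item.
- 3 items x 1 category = 3 points.

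This shows only how fine the target is on the scale. It is a difference between group means, so a bias of that size would have to be the average net shift over a whole arm.

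**5. What an assumed bias would do**

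Assume no true effect, a two-sided 5% test of two means, and a sample just large enough for 80% power at 2.9 points. Let the MCTV arm report b points better only because it knows its group. The test statistic then shifts by (1.960 + 0.842) x b / 2.9. The standard deviation cancels, because the required n grows with its square.

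| Assumed b (points) | Shift | Chance of p < 0.05 |
|---|---|---|
| 0.5 | 0.48 | about 7.7% |
| 1.0 | 0.97 | about 16% |
| 1.45 (half the target) | 1.40 | about 29% |

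The values of b and their direction are assumptions; the article gives none.

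**6. Extra time in the MCTV arm**

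- From section 2.6: 48 - 45 = 3 min; 24 x 3 = 72 min; 72 / (24 x 45) = 6.7%.
- From Table 2, reading its eight rows as weeks, with four 60-s series and three rests: (12 x 270 + 6 x 300 + 6 x 330) s = 7,020 s = 117 min, or 10.8%.

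The two differ because Table 2 lists four 60-s series (240 s) beside a total of 180 s. Either way the added time is modest.

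**The case against.** **The label could mean assessor plus analyst.** Section 2.5 openly lists who is blinded, so nothing is hidden. That is true, and it is why the repair is a matter of wording. It does not rescue the label: section 2.1.2 does not define the term this way, and neither role protects an outcome that the participant rates herself.

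**Expectation is not shown to favour vibration.** Both arms receive an active, supervised programme three times a week, and what women are told at consent is not available here. This stands. The bias is plausible, but the documents establish neither its size nor its direction.

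**A reader might infer that vibration is confounded with extra minutes and the squat, so that the comparison is invalid.** The article does not support this. Its stated question, in the Abstract, Introduction and Conclusions, is what WBV adds to MCT, and section 2.6.1 makes the squat part of how WBV is delivered. For an add-on question the posture and the few extra minutes belong to the package. They limit only a claim about vibration in isolation. Nor does the Discussion attribute a result to vibration: it states an expectation before any data exist.

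**A reader might ask for stronger remedies.** Having controls stand on a switched-off platform would match posture and time, but the women would still know there was no vibration, and it would change the control regimen. Requiring Biodex and functional reach to agree with FES-I before claiming efficacy would add an undefined success condition and change power. Neither is needed to correct what is wrong.

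**Conclusion.** The point holds. The double-blind label is contradicted by the article's own blinding and intervention sections: the design is assessor- and analyst-blinded. The consequence falls on both primary outcomes, because the unblinded participant is their rater at every post-baseline assessment.

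That participants are unblinded is an inference, but a firm one, since one arm stands on a vibrating platform and the other does not. The effect on the result cannot be sized from the documents. The range of 7.7% to 29% shows sensitivity under assumed biases and is not an estimate.

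The add-on comparison itself is legitimate. What needs limiting is the description of the blinding and the reach of the conclusion.

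**What to change.** 1. In section 2.1.2, replace the double-blind label with: *assessor- and analyst-blinded; participants and therapist not blinded*.
2. State the contrast as *MCT plus WBV delivered in a platform squat versus MCT alone*, so that conclusions refer to the add-on package and not to vibration in isolation.
3. In the Limitations, add that both primary outcomes are self-reported by participants who know their allocation. Say that they will be interpreted beside the assessor-measured Biodex fall-risk index and functional reach, which Table 3 already schedules at every assessment. These are supportive evidence, not a formal success condition, and they still depend on the participant's effort.

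The cost is three text edits, with no change to procedures, sample size or analysis.

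Separately, the 180-s total and the four 60-s series in Table 2 contradict each other and must be reconciled by the investigators.

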### 2.2. Participants

Participants will be recruited from the local community. Inclusion criteria are: (1) Elderly women over 60 years old with OST (diagnosed with Bone Densitometry Exam); (2) history of falls (at least two episodes in the last 12 months); (3) medical statement allowing the practice of physical exercise (cardiologic statement); (4) not participating in other research studies. Patients with: (1) Neurological diseases; (2) cognitive deficit (cognitive ability to respond and perform the exercises assessed by the Mini-Mental State Examination; MMSE), elaborated [26] and translation/modification proposed [27], using as a cutoff point for illiterate individuals = 19 points [28,29]; (3) severe Visual Impairment; (4) circulatory diseases; amputation or use of lower limb prosthesis; (5) history of recent fracture in the upper and lower limbs; (6) hernia, discopathy or severe spondylosis; and (7) neoplasm.

### 2.3. Recruitment

The project will be developed at the Laboratory of Kinesiotherapy and Manual Therapeutic Resources (Laboratório de Cinesioterapia e Recursos Terapêuticos Manuais; LACIRTEM) and at the Clinic School of the Department of Physiotherapy (Departamento de Fisioterapia; DEFISIO) at the Universidade Federal de Pernambuco (UFPE). Participants will be recruited at the Clinic School of DEFISIO, at the outpatient clinic of Clinic Hospital (Hospital das Clínicas; HC), at the Elderly Care Center (Núcleo de atenção ao idoso; NAI), at the Open University for the Elderly (*Universidade Aberta à terceira Idade*; UNATI-UFPE), and through dissemination on social and events aimed at the elderly. Those eligible and who express the intention to participate in the study, by signing the Free Consent Term, will undergo the initial interview after this recruitment.

### 2.4. Randomization and Allocation

Eligible participants will be randomized, by a researcher that is not involved in this study, through the Randomization website (www.randomization.com) into two groups: MCTV (intervention group) and MCT group (control group). Afterward, the list will be kept confidential, in which the order of the participants will be determined through numbered, sealed, and opaque envelopes that will only be opened when the intervention begins. The flowchart of participants and randomization is displayed, as shown in Figure 1.

### 2.5. Blinding

Outcome assessments will be performed by three researchers who are blind to the intervention group to which the participant was allocated. Statistical analysis will also be performed by a researcher who is blind to other research procedures.

### 2.6. Intervention

The intervention protocol will be applied by an experienced physical therapist, blind to the assessment of outcomes, soon after the enrolment period. It will consist of 8 weeks of training for both groups, totaling 24 sessions distributed three times a week, on alternating days. Each session will last between 45 and 48 min, depending on the participant’s group (Table 3).

#### 2.6.1. MCTV Group Intervention Description

This group will carry out the proposed WBV protocol combined with the MCT.

Multicomponent training should include cardiorespiratory and aerobic endurance; strength and flexibility; balance and body stability [30], flexibility not being mandatory as an MCT adequacy. Training should last 45 min, with 10 min warm-up, 30 min of the circuit, and 5 min of cool down [31,32]. It will consist of three stations: 1. cardiorespiratory and aerobic resistance; 2. strength, endurance, and flexibility; and 3. balance and body stability. The multicomponent stations will be distributed progressively as follows: (I) First station: free walking exercises will be performed on a treadmill; (II) second station: strengthening of upper and lower limbs with load progression will be performed; trunk and abdominal training and exercises in diagonal movements of the upper limbs; (III) third station: balance progression exercises will be performed, evolving different supports in orthostatic position (bilateral or unilateral), with a change of base and support surface (with and without eye-opening; in soil and foam) and balance training with a circuit.

The MCT will follow the prescribing principles under the ACSM Guidelines regarding the intensity, frequency, modality, and duration of each. The intensity during training will be regulated using the Borg Rating of Perceived Exertion scale, through which it is possible to measure the perceived exertion rate during exercise. The scale ranges from 6–20 points [33,34]. According to the individual’s fitness level, the exercises will be performed with a perceived effort between 10 and 16 points, respecting a weekly progression.

During the intervention, peripheral oxygen saturation (SpO2), heart rate (HR), and blood pressure (BP) will also be monitored.

For the aerobic exercise intensity, an incremental protocol will be used, with increased intensity every week, according to the perceived exertion rate. The intensity of the strengthening training stimulus will be incremental, with a slight to strong intensity variation as the weeks progress. It will be initially set at 40% of 1 RM (maximum repetition), with variation up to 70% of 1 RM. The intensity will be gradually progressed, as the weeks progress, being distributed as follows: one set of 10 repetitions in the first week, going to two sets of 10 to 15 repetitions

Balance activities will include static and dynamic exercises with the progression of postures as training progresses. All exercises in the program will be performed slowly to ensure the subjects’ safety, emphasizing good posture, social interaction, and pleasure [25].

Participants will perform the WBV on a vibrating platform after the end of the TMC. The vibration training will be carried out on the vibration platform KIKOS P204–110V (São Paulo, Brazil), whose vibration is of the lateral–lateral and oscillatory type. There will be 24 vibration sessions with an incremental increase of progressive frequency from 12.6 Hz to 30 Hz, the oscillation amplitude of 4 mm from peak to peak, lasting 60 s, and with a rest time of 10 to 30 s. Participants must, at the time of vibration, for better fixation of the feet on the board, perform the vibration with a silicone pad for the heels (made of non-slip material), so that only the forefoot and midfoot are in direct contact with the platform, to reduce the transmission of vibrations to the head, and a squat position of 100° will be adopted (considering 180° as total knee extension) in Figure 2. 

